#### Perception of Ethics and Accountability

After the intervention with ChatGPT, the students will be asked to fill out a web-based survey about their perception of their AI experience. The survey will use multiple-choice questions, short open questions and a 5-point Likert scale, using closed-ended response options. This response format ensures enhanced objectivity and enables appropriate discrimination to address the research objectives effectively. A closed-ended Likert scale also promotes the participants’ comprehension and active engagement with the study. The questionnaire consists of four sections: (1) a sociodemographic information; (2) AI literacy exploration of positive learning experiences with AI; (3) an examination of negative experiences associated with AI use; and (4) an assessment of the potential for discussing accountability, fostering student leadership, and addressing ethical and equity concerns pertaining to the use of AI. One question of this survey was taken from a Swedish questionnaire about the use and views among university students about chatbots and other AI for learning. Qualtrics software will be used for survey design and data collection, as this software passed a security assessment of Carleton University, and its server is located in Montreal, Quebec, Canada.

The SUS survey is expected to take approximately 2 minutes to complete, whereas the perception survey is anticipated to be completed in approximately 10 minutes. By collecting data at multiple points in the study (2 points), we can evaluate the effects of each intervention and any potential carryover effects during the crossover period. In addition, it provides an opportunity to measure changes in outcomes within individual participants as they switch from one intervention to another.

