### Control Intervention

In this study, the control intervention is the use of conventional web-based tools by students to complete the assignment. In this intervention, they will receive instructions on how to complete the assignment using conventional web-based tools available on the internet, without the use of ChatGPT or other generative AI platforms “and” or “or” tools. They will have a timeframe of 6 days to complete the assignment using these conventional web-based tools. Similar to the participants in the experimental intervention, they will also be required to fill out a survey on technology usability, providing feedback on their experience with the web-based tools.

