### Outcomes and Measurements

The outcome measures will be (1) the usability of the technological tools (ChatGPT or conventional) for completing the assignments (primary outcome), (2) the participants’ perception of these tools as support for learning, and (3) the learning outcomes (secondary outcomes). Outcomes and measurements will be collected at 2 points: at the first follow-up, that is, after the first intervention (experimental or control) in the initial phase, and at the second follow-up, that is, after the second intervention (experimental or control) in the final phase (Figure 1).

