#### Usability

Participants in the experimental intervention (AI-ChatGPT intervention) will also be asked to fill out a survey regarding their perception of using generative AI as an assistance tool to complete their assignments. This survey aims to gather insights into their thoughts, opinions, and attitudes toward using AI in their learning experiences. Participants will have the opportunity to share their feedback on the effectiveness, benefits, challenges, and overall satisfaction while using AI for assignment completion. Their responses will provide valuable information on AI technology’s perceived value and acceptance in enhancing their learning experience. Participants in the control intervention (conventional tools) will complete the same survey, but regarding the usability of the conventional tools.

The System Usability Scale (SUS) will assess the participants’ perceptions of usability. The SUS is a valid questionnaire [26] and will be administered at the end of the interventions and when participants cross over to the other assistance tool (AI-ChatGPT or conventional web-based tools without AI). The SUS is commonly used in numerous studies to assess the effectiveness and usability of new technologies, including in the education field [27-29]. A recent systematic review of home-based telerehabilitation software systems for remote supervision revealed that the SUS tool was the most frequently used measure or tool across the studies examined [28]. This scale has been translated into several languages, including the American Sign Language [30-32]. The SUS questionnaire was originally developed as a “quick and dirty” tool, with the goal of providing a fast and nonintrusive assessment experience for participants [26]. The SUS consists of 10 items formulated as affirmative statements, for which users indicate their level of agreement or disagreement on a 5-point Likert scale (1=strongly disagree; 5=strongly agree). For the odd answers (1, 3, and 5), we will subtract 1 from the score that the user answered; for the even answers (2 and 4), the score will be subtracted from 5. The values of the 10 questions will be added and multiplied by 2.5. The final score can range from 0 to 100. Internal consistency will be calculated using Cronbach α per item and overall. This scale allows for the assessment of outcomes and comparisons within and between the 2 interventions (Table 1).

**Table 1 table1:** Overview of outcome measures.

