### Data Analysis

This study aims to compare the 2 interventions in terms of usability, student perception, and learning outcomes. The crossover design allows for within-group and between-group comparisons, enabling a comprehensive analysis of students’ perceptions of the use of the intervention and its impact on their learning, as well as the effects of the intervention on their learning outcomes.

The use of an identification code will anonymize data. The data set will be exported from the datasheet and imported into the SPSS software (version 28.0; IBM Corp) for Mac, where the data will be subjected to analysis with a confidence level of 95%. Descriptive statistics, including the calculation of frequencies, will be performed on the sociodemographic variables of the students. The usability scale and grades at each assessment time will be summarized using mean and SD. The nonparametric Wilcoxon test will be used to compare the differences between these variables.

The frequencies, means, and SDs of each item of the SUS scale will be calculated and compared using the McNemar or chi-square and Wilcoxon tests, respectively. In addition, the usability scores and the grades of each group will be correlated using Spearman correlation.

For the analysis of perception and usability outcomes, we will use the Spearman correlation coefficient to assess the relationship between the 2 scales. This statistical approach was chosen to measure the strength and direction of the associations between variables when the data may not conform to a linear pattern. Using the Spearman correlation coefficient, we aim to better understand how perceptions and usability factors are interrelated, providing a robust basis for our research findings and conclusions. To assess the internal consistency of the scales, Cronbach α coefficient will be calculated for both constructs and for each individual item.

To categorize the students into groups of low and high performance (using a cut-off value of 80) and classify the SUS scale into high and low usability groups (with a cut-off value of 50), appropriate statistical tests will be applied. Specifically, Fisher exact test or Pearson chi-square test will investigate the associations between the categorized scales and sociodemographic characteristics.

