## Results

Data collection took place in October and November 2023; the anticipated results are scheduled for publication in 2024. We anticipate several key findings. First, randomization is expected to have groups with closely matched demographic characteristics, ensuring a balanced starting point for our analysis. Second, we anticipate that usability will be significantly higher for the ChatGPT intervention than for conventional methods, reflecting the potential benefits of AI-assisted learning. In addition, regarding ChatGPT’s use in assignments, we expect to observe students expressing concerns about data privacy and plagiarism, consistent with prior literature findings on these issues. The potential correlation between usability and learning outcomes is a significant aspect to consider in our study. Understanding how usability impacts learning outcomes not only is critical for this study but also lays the foundation for future investigations. By quantifying the effect sizes of both the learning and usability effects in this study, we can better inform the calculation of sample sizes for larger RCTs on this topic. These data will be invaluable for designing robust experiments and ensuring that our research can provide meaningful insights into the relationship between usability and educational outcomes.

Furthermore, it is our anticipation that despite these concerns, learning outcomes will remain consistent across both interventions. We expect to observe that while these concerns may be raised, the overall effectiveness and educational benefits of ChatGPT are not compromised. Our study seeks to determine whether these anticipated results are confirmed. These data will contribute to a better understanding of the potential impacts of integrating AI into health sciences education.

This study is expected to contribute to the identification of key areas and challenges concerning the use of AI as an educational tool, specifically examining its benefits and challenges for students. By doing so, it aims to facilitate the establishment of comparable frameworks for future academic endeavors. In addition, the findings will enlighten educators about the potential advantages and barriers associated with integrating AI into educational activities for university students.

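### Sociodemographic items sit in the post-ChatGPT survey, so which randomized students supply them depends on sequence (minor)

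*Protocol article*

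**What the plan says.** All references are to the protocol article.

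- **Perception of Ethics and Accountability** fixes the timing: "After the intervention with ChatGPT, the students will be asked to fill out a web-based survey about their perception of their AI experience". It also fixes the content: "The questionnaire consists of four sections: (1) a sociodemographic information; (2) AI literacy exploration of positive learning experiences with AI". Table 1 lists the same four sections.
- **Outcomes and Measurements** names two time points, each following an intervention: "Outcomes and measurements will be collected at 2 points: at the first follow-up, that is, after the first intervention", and then the corresponding point after the second intervention. No point before randomization is named.
- **Control Intervention** gives control-period students a usability survey: "they will also be required to fill out a survey on technology usability, providing feedback on their experience with the web-based tools".
- **Usability** describes a survey on generative AI and continues: "Participants in the control intervention (conventional tools) will complete the same survey, but regarding the usability of the conventional tools".
- **Recruitment** has an invitation to the Qualtrics questionnaires go out once a student consents. It does not say which questionnaires open then. The same section gives their purpose as learning about the student's experience while doing the assignments.
- **Data Analysis** plans descriptive frequencies of sociodemographic variables. It also plans Fisher or chi-square tests that "will investigate the associations between the categorized scales and sociodemographic characteristics", the scales being grade cut at 80 and SUS cut at 50.
- **Results** anticipates demographic balance: "First, randomization is expected to have groups with closely matched demographic characteristics, ensuring a balanced starting point for our analysis".

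**The concern.** Characteristics that describe who was randomized are best recorded before randomization, so that they exist for everyone regardless of what follows. Here the stated place for them is a survey that each sequence reaches at a different time. A BA student who leaves between periods has a period-1 grade and a period-1 SUS score but no sociodemographic record. An AB student who leaves at the same moment has already given one.

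Two things are at stake. The association tests would run on a subset whose make-up depends on sequence. And the expectation of demographic balance could be examined only among students who reached and answered the post-ChatGPT survey, not among all who were randomized.

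**Working it through.** **Inputs.** Sample size 45 plus a 10% allowance for loss between interventions, giving 50 (Sample Size). Allocation 1:1 (Randomization and Allocation Concealment). Each period lasts 6 days (Experimental Intervention, Control Intervention). Washout is 21 days (Washout Period).

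**The plan's own figure.** 45 / 0.90 = 50, and 45 × 1.10 = 49.5, which rounds up to 50. The stated total reproduces either way. At 1:1 this is 25 AB and 25 BA.

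**Timing, if the survey follows ChatGPT only.**
- AB: end of period 1, about day 6.
- BA: 6 + 21 + 6 = about day 33.
- Gap: 33 − 6 = 27 days.

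**Missing sociodemographics from loss between periods.** Assume the loss is even across sequences and that everyone still present answers.
- Total lost: 0.10 × 50 = 5, or 2.5 per sequence.
- AB without sociodemographics for this reason: 0 of 25, because they answered before leaving.
- BA without sociodemographics: 0.10 × 25 = 2.5 of 25, that is 2 to 3 students, or 2.5 / 50 = 5% of the trial.
- Sensitivity to the loss rate: at 5%, 1.25 BA students; at 20%, 5 BA students.
- Extreme split: if all 5 losses at the 10% rate fell in BA, 5 of 25 = 20%. Nothing in the article suggests such a split.

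**Where the loss falls in the association tests** (same assumptions, and taking loss to mean that no period-2 data are supplied).
- ChatGPT-period records: 25 AB + 22.5 BA = 47.5, all with sociodemographics.
- Conventional-tool records: 22.5 AB + 25 BA = 47.5. Those with sociodemographics: 22.5 + 22.5 = 45.
- So the 2.5 records removed are all conventional-tool records from BA students.

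**The passages side by side.** Three readings of when the sociodemographic section is answered:

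1. *After ChatGPT only.* This is the plain text of the perception section and Table 1. It fits Control Intervention, which describes a usability survey, and the separate completion times given for the SUS (2 minutes) and the perception survey (10 minutes). The figures above apply.
2. *After both periods.* This takes the Usability sentence about control participants to cover the whole perception survey. Both sequences would then answer at about day 6 and the sequence-related loss between periods would vanish. Collection would still follow a randomized intervention.
3. *At consent.* This takes the Recruitment invitation to open a baseline form. Nothing would be missing for this reason. But the purpose stated in that section does not describe a baseline form, and neither the perception section nor Table 1 mentions one.

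Reading 1 is the best supported, but the text does not exclude the other two.

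**The case against.** The strongest reply is that the article never says these items are collected nowhere else. Recruitment and Usability leave room for earlier collection, the two stated time points concern outcomes, and a short enrolment form is the kind of detail a condensed article may leave to the full protocol. This stands in part: that the post-ChatGPT survey is the only source is an inference. But the article is not silent. It assigns the sociodemographic section to a named survey at a named time, and that assignment is what needs reconciling.

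Other objections stand, and they rule out stronger readings that a reader might infer:

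- *That ChatGPT use contaminates the demographics.* Typical sociodemographic items would not change during a 6-day assignment or over 27 days. The item list is not given, so this is an assumption, but a safe one.
- *That AI literacy is misused as a baseline variable.* It belongs to the secondary perception outcome, and no planned analysis uses it as a baseline covariate or moderator.
- *That a planned balance check is invalid.* Data Analysis plans no table by sequence and no balance test. The Results sentence is an expectation.
- *That the primary result is biased.* The SUS comparison is within student. A BA student lost before period 2 has no ChatGPT score to pair, so a missing sociodemographic record costs that comparison nothing.

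Finally, Results states that data were collected in October and November 2023, so moving the questions may no longer be possible.

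**Conclusion.** The concern holds as a minor point. As written, sociodemographics come from the post-ChatGPT survey, no pre-randomization collection is described, and the sections on recruitment, usability and perception do not settle whether any takes place. The consequence is missingness that depends on sequence: about 2 to 3 of 25 BA students against 0 of 25 AB students, with the two sequences surveyed about 27 days apart. This rests on 50 students randomized 1:1, the plan's 10% loss falling evenly between periods, full response from those remaining, and the survey being given after ChatGPT only. It affects the descriptive and association analyses and what can be said about balance among all randomized students. It does not change the sample size or bias the primary paired SUS comparison.

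**What to change.** Reconcile Recruitment, Usability, Control Intervention, Table 1 and the perception section, so that one statement says when the sociodemographic section is answered and by whom.

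If the items can still be placed, collect them in a short Qualtrics form at consent, before randomization, with any prior-AI-use items as an optional addition. Keep the experience and ethics sections after ChatGPT, and describe all randomized students by sequence. This brings the sequence-related loss to 0 and costs almost nothing, since most of the questions already exist.

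If collection is closed and consent-stage data exist, say so and correct the perception section and Table 1. If none exist, report the items as collected post-intervention, give the number missing by sequence, and do not present them as evidence of balance among all randomized students. That costs only a few sentences in the report.

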### Data Analysis

This study aims to compare the 2 interventions in terms of usability, student perception, and learning outcomes. The crossover design allows for within-group and between-group comparisons, enabling a comprehensive analysis of students’ perceptions of the use of the intervention and its impact on their learning, as well as the effects of the intervention on their learning outcomes.

The use of an identification code will anonymize data. The data set will be exported from the datasheet and imported into the SPSS software (version 28.0; IBM Corp) for Mac, where the data will be subjected to analysis with a confidence level of 95%. Descriptive statistics, including the calculation of frequencies, will be performed on the sociodemographic variables of the students. The usability scale and grades at each assessment time will be summarized using mean and SD. The nonparametric Wilcoxon test will be used to compare the differences between these variables.

The frequencies, means, and SDs of each item of the SUS scale will be calculated and compared using the McNemar or chi-square and Wilcoxon tests, respectively. In addition, the usability scores and the grades of each group will be correlated using Spearman correlation.

For the analysis of perception and usability outcomes, we will use the Spearman correlation coefficient to assess the relationship between the 2 scales. This statistical approach was chosen to measure the strength and direction of the associations between variables when the data may not conform to a linear pattern. Using the Spearman correlation coefficient, we aim to better understand how perceptions and usability factors are interrelated, providing a robust basis for our research findings and conclusions. To assess the internal consistency of the scales, Cronbach α coefficient will be calculated for both constructs and for each individual item.

To categorize the students into groups of low and high performance (using a cut-off value of 80) and classify the SUS scale into high and low usability groups (with a cut-off value of 50), appropriate statistical tests will be applied. Specifically, Fisher exact test or Pearson chi-square test will investigate the associations between the categorized scales and sociodemographic characteristics.

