**Secondary**				
	Perception of AI^c^	Continuous, nominal, ordinal, and 5-point Likert-type scale	The questionnaire consists of four sections: (1) sociodemographic information; (2) AI literacy exploration of positive learning experiences with AI; (3) examination of negative experiences associated with AI use; and (4) an assessment of the potential for discussing accountability, fostering student leadership, and addressing ethical and equity concerns pertaining to the use of AI.	Fisher exact or Pearson chi-square test will investigate the associations between the categorized scales and sociodemographic characteristics.
Learning outcomes		Continuous	Students’ grades on both interventions. Score range (0-100)	Mean, SD

^a^SUS: System Usability Scale.

^b^5=Strongly agree, 4=agree, 3=neither agree nor disagree, 2=disagree, and 1=strongly disagree.

^c^AI: artificial intelligence.

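### The plan promises effect sizes for usability and learning, but its stated outputs include no tool difference, no interval for it and no SD of the within-student difference

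*Protocol article*

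**What the plan says.** The aim is in the Results section of the protocol article: "By quantifying the effect sizes of both the learning and usability effects in this study, we can better inform the calculation of sample sizes". The trials meant are future, bigger randomized ones. The same section anticipates that learning outcomes will not differ between the tools, and says the study is to establish whether its expectations are borne out.

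The outputs are in Data Analysis. For SUS and grades: "The usability scale and grades at each assessment time will be summarized using mean and SD". Then: "The nonparametric Wilcoxon test will be used to compare the differences between these variables". The text does not say whether this is the signed-rank or the rank-sum form. In Table 1 the learning outcome is described as "grades on both interventions. Score range (0-100"), and its analysis column gives mean and SD only.

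The other planned analyses are SUS item summaries and tests, Cronbach α, Spearman correlations ("the usability scores and the grades of each group will be correlated using Spearman correlation") and Fisher or chi-square tests on categorized scores. A 95% level appears once, in the sentence on software: "where the data will be subjected to analysis with a confidence level of 95" per cent. It is attached to no estimate.

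On timing, Outcomes and Measurements says: "Outcomes and measurements will be collected at 2 points: at the first follow-up, that is, after the first intervention (experimental or control"), and again after the second. The section Perception of Ethics and Accountability says of the two measurements that "it provides an opportunity to measure changes in outcomes within individual participants as they switch from one intervention to another". No within-student quantity is then listed as an output.

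**The concern.** In a two-period crossover, the tool effect and its precision come from each student's own difference between tools. The aim in Results needs that difference for SUS and for grades, with a measure of its uncertainty. None of the outputs in Data Analysis or Table 1 is that quantity. A Wilcoxon test gives a p-value, not a difference in SUS or grade points. Spearman correlations describe how usability and grades move together, not what the tool does.

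Two things are at stake. First, the trial could finish without saying how much the tools differ or how well that is known. Similarity of grades would then rest on a non-significant rank test, which cannot show similarity. Second, a later trial that again pairs students would lack the variance it needs.

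**Working it through.** **Figures in the plan.** The plan states no effect size or interval that could be reproduced. The only figure used here is its 45 evaluable students, raised by 10% to 50 (45 × 1.10 = 49.5, rounded up). The Fleiss formula with continuity correction for 84% against 50%, two-sided 5% and 90% power gives 44 per group, close to the stated 45. Whether a per-group figure may serve as the total is a separate matter. Below, 45 is simply the number of complete pairs.

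**Step 1. What summaries by assessment time show.** Allocation is 1:1 to AB or BA, so each assessment time contains both tools. Take an invented example with a base of 60, a tool effect of 10 and a period effect of 5.

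| Sequence | Time 1 | Time 2 |
|---|---|---|
| AB | 70 (ChatGPT) | 65 (conventional) |
| BA | 60 (conventional) | 75 (ChatGPT) |

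- By time, equal sequences: (70 + 60)/2 = 65 and (65 + 75)/2 = 70. The difference of 5 is the period effect; the tool effect has cancelled.
- By tool, equal sequences: (70 + 75)/2 = 72.5 and (65 + 60)/2 = 62.5. The difference of 10 is the tool effect.
- By tool, sequences of 25 and 20: (25×70 + 20×75)/45 − (25×65 + 20×60)/45 = 72.2 − 62.8 = 9.4. A little of the period effect leaks in.
- Allowing for period: half the difference between the sequences in mean time-1-minus-time-2 change, [5 − (−15)]/2 = 10, whatever the sequence sizes.

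So the layout decides whether a point estimate can be recovered at all.

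**Step 2. What marginal SDs leave out.** Let both tools have SD s and let r be the within-student correlation. The SD of the paired difference is s√(2(1 − r)), and the 95% CI half-width with 45 pairs is t(0.975, 44) × that SD / √45, with t = 2.015. Neither s nor r is in the documents; s = 20 SUS points is assumed.

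| r | SD of difference | Half-width |
|---|---|---|
| 0 | 28.3 | 8.5 |
| 0.5 | 20.0 | 6.0 |
| 0.8 | 12.6 | 3.8 |

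The same published marginal SDs fit all three rows. For grades the half-widths scale with their SD: about 0.42s, 0.30s and 0.19s.

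**Step 3. Sizing a later trial.** Assume a 5-point SUS target, two-sided 5% and 90% power.

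- Crossover total: ((1.96 + 1.2816) × SD of difference / 5)² = 337, 169 or 68 for the three rows.
- Parallel, per arm: 2 × ((1.96 + 1.2816) × 20 / 5)² = 337, whatever r is.

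The spread therefore arises only if the later trial is a crossover.

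**The case against.** The strongest reply is that much of this is detail a full analysis plan would hold. The article does say that effect sizes will be quantified, mentions change within participants, and nowhere says its list of outputs is exhaustive. The effect-size aim also stands in the anticipated results, not among the objectives or hypotheses. The last point is true and tempers the weight of the finding. The first goes only so far: Data Analysis is specific down to tests, software version and cut-off values, and the outputs it names for SUS and grades do not match the use announced for them.

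Three stronger readings are tempting, and the documents do not support them.

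- A reader might infer that the planned outputs can yield no tool effect at all. Table 1 refers to grades under both interventions, and the study groups are defined by tool. If the means are split that way, subtraction gives a raw estimate, and dividing by the marginal SD gives a legitimate standardized one. What is missing is its precision.
- A reader might infer that no later trial could be sized. The article does not say which design the larger trials would have, and a parallel trial can be sized from the marginal SD.
- A reader might convert a borderline p-value into a range of 3.8 to 8.5 SUS points. That uses a paired t calculation, not the planned Wilcoxon test, and is at best approximate.

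It is also fair that a signed-rank statistic could be turned into a rank-based index, or used with a mean difference to approximate the paired SD. But the form of the test is not stated, the index is not in SUS or grade points, and the back-calculation is rough where direct reporting is easy.

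**Conclusion.** The point holds as a mismatch between a stated aim and the stated outputs. Data Analysis and Table 1 name no ChatGPT-minus-conventional difference in SUS total or grades, no confidence interval for it, and no SD of the within-student difference. Read literally, summaries by assessment time contrast periods rather than tools. Read by tool, they allow a point estimate without its precision.

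For scale, the unreported correlation moves the half-width between 8.5 and 3.8 SUS points. This rests on equal SDs of 20, 45 pairs and correlations from 0 to 0.8, all assumed except the 45. The consequence is for the trial's own interval, for its expected finding of similar grades, and for a later crossover. It does not extend to a later parallel trial. The change should be made, but nothing here undermines the design or the data.

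**What to change.** In Data Analysis and Table 1:

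- Summarize SUS total and grades by tool and period.
- For each, report the paired ChatGPT-minus-conventional difference with a 95% CI, allowing for period. Use the mean difference, or the Hodges-Lehmann estimate if the signed-rank test is kept, so that estimate and test correspond.
- Report the SD of the within-student differences or the within-student correlation.

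In Results, say that later trials will be sized from these quantities and name the design meant. Base any statement that learning outcomes are similar on the interval for the grade difference, not on a non-significant test.

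The cost is a few sentences, a revised Table 1 entry and a little more analysis. The article reports that data collection is complete; everything needed is in the planned dataset, so no new data are required.
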